# Better Use of Data to improve parent Satisfaction (BUDS): protocol for a prospective before-and-after pilot study employing mixed methods to improve parent experience of neonatal care

**DOI:** 10.1136/bmjpo-2019-000515

**Published:** 2019-06-25

**Keywords:** neonatology, patient perspective, qualitative research

## Abstract

**Introduction:**

Having a baby that requires neonatal care is stressful and traumatic. Parents often report dissatisfaction with communication of clinical information. In the UK neonatal care data are recorded daily using electronic patient record systems (EPR), from which deidentified data form the National Neonatal Research Database (NNRD). We aim to evaluate the impact of sharing neonatal EPR data with parents, on parent-reported satisfaction, parent–staff interactions, staff workload and data completeness.

**Methods:**

A prospective, before-and-after, mixed-method study. Participants are parents of inpatient babies (maximum 90) and staff in a tertiary neonatal intensive care unit, London, UK. The intervention was developed by former neonatal parents, neonatologists and neonatal nurses: a communication tool for parents comprising individualised, written, daily infant updates for parents, derived from EPR data. The intervention will be provided to parents over 6 weeks. Plan-Do-Study-Act cycles will inform the tool’s iterative development and improvement. The tool’s impact will be measured using a validated parent survey, staff survey, data completeness measures and interviews.

**Analysis:**

Primary outcome: parent satisfaction ‘with communication of clinical information and involvement in care’. Secondary outcomes: parent–staff interactions, staff workload, data completeness. Baseline survey data will be obtained from clinical service evaluation preceding the intervention. Baseline data completeness will be derived from the NNRD. During the intervention, surveys will be administered biweekly and data completeness assessed daily. We will analyse outcomes using run charts and partially paired statistical tests. Parent and staff interviews will explore information exchange and the communication tool’s impact.

**Discussion:**

This study will evaluate the impact of a parent co-designed intervention on communication with parents in neonatal care and the completeness of routinely recorded electronic clinical data. Better use of routinely recorded clinical data provides the opportunity to improve parent satisfaction and increase the research utility of such data, benefiting clinical care.

**Ethics and dissemination:**

Reviewed and approved by the West Midlands—South Birmingham REC (18/WM/0175).

**Registration number:**

ISRCTN62718241.

What is known about the subjectNeonatal care significantly affects parents’ mental health, infant development and outcomes.Parent satisfaction is increasingly used as a parent experience measure and is commonly assessed using invalidated questionnaires.Interventions aimed at improving parent satisfaction traditionally do not involve parents in their design.

What this study hopes to addInterventions co-designed with parents receiving National Health Service (NHS) neonatal care have the potential to improve parent satisfaction.Using a validated parent satisfaction questionnaire for outcome measurement adds to the validity of results and enables comparison with other interventions.Implementing an intervention using routinely recorded infant data has the potential to make it sustainable and generalisable across NHS neonatal care.

## Introduction

One in eight UK newborn babies will require hospital care on a neonatal unit.^1^ This can be traumatic for parents, who often report it is difficult to obtain clinical information from staff^2^ and feel excluded from their baby’s care. Anxiety, depression and post-traumatic stress disorder symptoms have been reported in as high as 35% of parents following neonatal care^3 4^ and this stress has been shown to interfere with parent–child attachment and bonding.^5^ Improving parent experience in neonatal care can reduce parent stress, potentially improving parent–child bonding^5^ and infant outcomes.^6^ Parent satisfaction is inversely related to stress^7^ and is increasingly used as a parent experience measure and service quality indicator to inform high quality neonatal care.^8^

The latest national UK survey of parents’ neonatal experiences found that ‘parent satisfaction with receiving clinical information’ and ‘feeling involved in babies’ care’ were among the lowest scoring of all areas evaluated.^2^ Improving the quality and quantity of communication between parents and neonatal staff benefits patient care, promotes positive parent–child interaction and improves wider family well-being and satisfaction.^9 10^ There is evidence that parent satisfaction can be improved through simple interventions, such as providing written information to parents,^11 12^ however, previous interventions required additional work from staff to collect, record, collate and provide information to parents, limiting their sustainability and generalisability. Further limitations of previous studies include the failure to involve parents in study development and the use of invalidated questionnaires to measure the impact of interventions.^13^

The aim of this study is to use existing, routinely recorded data, from existing neonatal electronic patient record systems (EPR) to implement, further co-develop and evaluate a neonatal communication tool with parents. In the UK a defined set of data items are extracted from neonatal EPR systems to form the National Neonatal Research Database (NNRD).^14^ This holds information on all babies admitted for NHS neonatal care and is used for audit, benchmarking and research, but is currently not routinely shared with parents. The completeness of data in the NNRD is high^14^ but has the potential to further improve. There is a lack of evidence for interventions to improve the completeness of routinely collected data in neonatal care and more widely.

We will evaluate the impact of sharing routinely recorded infant information with parents, on parent satisfaction with ‘communication of clinical information and involvement in care’ using a validated questionnaire, and on the completeness of NNRD data extracted from neonatal EPR systems. We hypothesise that sharing individualised, daily EPR data with parents will lead to higher reported parent satisfaction and data completeness.

## Methods and analysis

### Parent and public involvement and co-development of the communication tool

This study was conceived in response to the clinical need identified by parents with neonatal care experience; a partnership including families with experience of preterm birth identified ‘what emotional and practical support improves attachment and bonding, and does the provision of such support improve outcomes for premature babies and their families?’ as a top 10 research priority.^15^

Parents of babies previously requiring NHS neonatal care were directly engaged in the study design. During the preparatory phase, the shared aim of the study, proposed intervention and preliminary qualitative work were informed by parent focus groups. A study steering group for the Better Use of Data to improve parent Satisfaction (BUDS) project was formed, including neonatologists, a neonatal nurse, parent participants, representation from Bliss (the national charity for babies born premature or sick) and the NIHR CLAHRC NWL improvement science team. A project-planning meeting was held to identify the problem with parent satisfaction, set the project’s aim to improve it and discuss ways to achieve that. Potential techniques were identified by parents for parents, one of which was a communication tool to share daily written infant information with parents. Parents co-designed the communication tool and validated a parent satisfaction survey for use in this study through focus groups and cognitive testing interviews. Parents will continue to be involved, as an advisory group, throughout the study in line with the 4Pi National Involvement Standards for effective co-development.^16 17^

Further iterative development of the communication tool, involving parents, will continue during evaluation using improvement science methodology (discussed below). Our parent representative will be involved in drafting all study output reports and will be encouraged and supported to present our findings at conferences.

Once the trial has been published, we will co-develop parent-centred study reports with parents from our steering group and Bliss, to be disseminated by Bliss and via social media. Study participants will be informed of the results through the study’s website and via email in a study newsletter.

### Communication tool

We previously identified the information parents report as important when their baby is on a neonatal unit through qualitative work with ex-neonatal parents. This information was matched to the routinely recorded neonatal daily EPR data items and we developed parent-friendly explanations of these EPR data items with parents. We co-designed a communication tool template for parents called ‘*My Baby’s Summary Report*’; this comprised a printed sheet of paper including individualised, daily infant updates for parents derived from EPR data, in parent-centred language.

### Design

A prospective before-and-after study employing mixed methods. The intervention (the communication tool) will be implemented in stages across the three intensity unit areas of the Chelsea and Westminster hospital neonatal intensive care unit (from low to high) over an 8-week period; a 2-week proof of concept phase will precede a 6-week roll-out phase (figure 1). An individualised *‘My Baby’s Summary Report’* will be administered to recruited parents in a sealed envelope every weekday. Quality improvement methodologies, including Plan-Do-Study-Act (PDSA) cycles^18–20^ and run-charts^21^ will be used to implement and further improve the communication tool. The content and the exact timing of the implementation in relation to the study will be fully described to avoid other concurrent parent-centred interventions influencing our study results.

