#### Parents

The lead researcher will recruit parents of babies that are inpatients on the Chelsea and Westminster hospital neonatal unit by directly approaching them on the unit during their baby’s stay. This neonatal unit in London, UK, provides tertiary level neonatal intensive care, including specialist surgical care, with 750 annual admissions and a 36-cot capacity.

*Inclusion criteria:* We will start recruiting parents with babies in the lower intensity part of the unit for 4 weeks (Special Care Baby Unit- SCBU), who are medically stable and not acutely unwell. We will additionally recruit parents in the High Dependency Unit (HDU). area for 2 weeks and parents from the Intensive Care Unit (ICU) area for the final 2 weeks.*Exclusion criteria:* Parents that cannot speak and/or read English will be excluded as the study’s information documents and communication tool are in English. Parents younger than 16 years of age will be excluded.

Recruited parents will be asked to complete a demographic form including their age, gender, ethnic group, infant’s gestational age and infant’s length of stay on the neonatal unit.

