#### Stage 2: ‘Roll out’ (6 weeks—SCBU 2 weeks—HDU 2 weeks—ITU 2 weeks)

We will recruit a maximum of 90 parents, administer *‘My baby’s Summary Report’* every weekday and conduct a qualitative and quantitative evaluation over 6 weeks, while also using quality improvement methodology to further improve the communication tool (figure 2).

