### Analysis

#### Baseline measurement

Baseline measures for parent satisfaction and staff workload will be obtained from on-going evaluations undertaken as part of clinical service evaluation on the neonatal unit; these evaluations use the PEC survey and staff survey. Data from PEC and staff surveys from a 6-week period before the start of the trial will be used to generate baseline median values for each PEC survey item and staff survey questions using run charts (21).

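### The tool is rolled out by intensity area, but the baseline, run charts and before-after comparison are not split by area, so part of any apparent change can reflect who was surveyed

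*Protocol article*

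**What the plan says.** The Design section describes "A prospective before-and-after study employing mixed methods". The tool "will be implemented in stages across the three intensity unit areas" of one hospital's neonatal unit, from low to high intensity.

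Two places describe the order, and they do not clearly agree:
- The Stage 2 heading reads "6 weeks—SCBU 2 weeks—HDU 2 weeks—ITU 2 weeks", which suggests one area after another.
- The Parents section says "We will start recruiting parents with babies in the lower intensity part of the unit for 4 weeks" (which fits the 2-week proof of concept plus the first roll-out fortnight). It continues "We will additionally recruit parents in the High Dependency Unit (HDU). area for 2 weeks", with ICU parents for the final 2 weeks. That wording can mean that areas accumulate.

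On the comparator, Baseline measurement says: "Data from PEC and staff surveys from a 6-week period before the start of the trial will be used to generate baseline median values". There is one such median per item. The source is "on-going evaluations undertaken as part of clinical service evaluation on the neonatal unit". No breakdown by area is given.

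Quantitative outcomes then uses run charts, and compares the baseline period with the intervention period using partially paired parent data. The demographic form in the Parents section covers age, gender, ethnic group, gestational age and length of stay, but not unit area. The Discussion commits to correcting for parent demographics. It names infant severity and changes in condition among the influences on responses that the study does not measure.

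On co-interventions, Design says that content and timing "will be fully described to avoid other concurrent parent-centred interventions influencing our study results".

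**The concern.** The areas are ordered by intensity of care, and so roughly by how ill the babies are. The protocol itself says that illness can influence survey answers. Opening the areas in that order ties a factor the authors believe affects the primary outcome to calendar time within the roll-out. The reference line on every run chart is meanwhile a single median that ignores area. A run chart could rise early and fall late, or start high and drift, because of who was surveyed and not because of the tool. Readers would tend to credit the tool, since the stated aim of this analysis is its specific impact. The study is also meant to inform a cluster RCT, so a case-mix artefact could be carried forward.

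The sentence on co-interventions adds to the problem. Describing concurrent changes helps a reader interpret the result but does not stop those changes from affecting it.

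**Working it through.** The documents give no SD, effect size, area means or area mix, only a cap of 90 roll-out parents. There is no stated figure to reproduce, so the check is structural, followed by an illustration on declared assumptions.

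**1. Area mix over the roll-out.** Shares are SCBU/HDU/ICU, with responses assumed proportional to area-weeks.
- Sequential: 100/0/0, then 0/100/0, then 0/0/100. Pooled (2, 2 and 2 weeks): 33/33/33.
- Cumulative: 100/0/0, then 50/50/0, then 33/33/33. Pooled (6, 4 and 2 weeks): 50/33/17.

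Within the roll-out, the correlation of area with fortnight is 1.0 under sequential staging and 0.5 under cumulative staging.

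**2. Spurious shift with no tool effect.** Assume mean satisfaction of 0 in SCBU, -d/2 in HDU and -d in ICU (SD units), and a baseline mix of 50/25/25.

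Baseline mean = 0.5 × 0 + 0.25 × (-d/2) + 0.25 × (-d) = -0.375d.

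Shift = mean under the roll-out mix minus (-0.375d). At d = 0.5:

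| Staging | Fortnight 1 | Fortnight 2 | Fortnight 3 | Pooled |
|---|---|---|---|---|
| Sequential | +0.375d = +0.19 | -0.125d = -0.06 | -0.625d = -0.31 | -0.125d = -0.06 |
| Cumulative | +0.375d = +0.19 | +0.125d = +0.06 | -0.125d = -0.06 | +0.042d = +0.02 |

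Sequential points for other gaps: +0.11, -0.04, -0.19 at d = 0.3; +0.30, -0.10, -0.50 at d = 0.8.

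**3. Scale against sampling error.** Assume 90 baseline respondents.
- One fortnight, sequential (90/3 = 30 v 90): SE = sqrt(1/30 + 1/90) = 0.21. At d = 0.5 the shifts are 0.19/0.21 = 0.9, 0.06/0.21 = 0.3 and 0.31/0.21 = 1.5 standard errors.
- Pooled (90 v 90): SE = sqrt(2/90) = 0.149. At d = 0.5 the shift is 0.06/0.149 = 0.4 (sequential) or 0.02/0.149 = 0.14 (cumulative) standard errors. At d = 0.8, sequential, it is 0.10/0.149 = 0.7.

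**4. Dependence on the assumed baseline mix.** With an equal-thirds baseline the baseline mean is -0.5d. Sequential points become +0.5d, 0 and -0.5d, and their pooled shift is 0. The cumulative pooled shift becomes -0.333d + 0.5d = +0.167d, or +0.08 SD at d = 0.5. With 90 v 90 and a two-sided 5% test, that gives about an 8% chance of a false signal of benefit, against a nominal 2.5% in that direction.

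**5. What area data would make estimable.** Take three baseline and three roll-out fortnights.
- With area effects and either no time effect or a linear one, exposure is estimable under both stagings, provided area is known in both periods.
- With a separate effect for each fortnight it is not (rank 8 for 9 columns), because everyone surveyed in a roll-out fortnight is exposed.

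Area can therefore be separated from the tool. Calendar time in general cannot.

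The illustration works on means. Medians of Likert items move in steps and may shift more or less than this.

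**The case against.** **The planned pairing may remove much of it.** Quantitative outcomes can be read as comparing changes from baseline to repeat measures between periods, and the Discussion stresses longitudinal baseline measures. On that reading, stable differences between areas largely cancel for parents who are paired. This stands for those parents, as long as the baby's area and condition do not change between surveys. It does not cover unpaired responses or the run charts.

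**A reader might infer that area, time and exposure are wholly aliased, so that the before-after result could be produced entirely by the order of areas.** The documents do not support this. Complete aliasing of area with time needs the sequential reading. Under the cumulative reading the last fortnight covers all three areas. That the baseline is unit-wide is itself an inference from the wording, as no mix is given. The pooled artefact is also small on the assumptions above. Setting single-fortnight shifts against the pooled standard error of 0.149 would make them look larger relative to noise than they are.

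**A reader might also infer that concurrent unexposed surveys are available and unused.** The service evaluation is called ongoing as the source of a pre-trial baseline. Nothing says it continues in unopened areas during the roll-out.

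**The limits are partly conceded.** The article acknowledges non-randomised bias, calls the study a small-scale pilot and collects gestational age and length of stay, which are partial proxies for acuity. Model terms are often left to an analysis plan. However, the article does state its adjustment and its form contents, and area is in neither. Nor does it mention that the surveyed population shifts by area.

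**Conclusion.** The point holds in limited form. Areas open in order of intensity, the comparator is a single median per item with no split by area, and the stated adjustment leaves area out. Run-chart points and unpaired contrasts therefore mix any tool effect with case mix, fully under sequential staging and partly under cumulative staging.

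The size is unknown. With d = 0.5 SD and a 50/25/25 baseline, single sequential fortnights could move by up to about 0.3 SD with no tool effect. That is roughly one and a half standard errors at an assumed 30 v 90. The pooled comparison would move by less than 0.1 SD, with a sign that depends on the staging and the assumed mix. The run charts are the more exposed part of the plan.

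Confounding with calendar time is inherent in this before-after design and is not removed by handling area. The claim that description prevents the influence of co-interventions is wrong as worded.

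**What to change.** 1. Record area (SCBU, HDU or ICU) on every PEC survey in both periods. Build baseline medians and run charts by area, and make the before-after comparison within area, with area as a fixed effect and the result pooled across areas.
2. Reconcile the Parents section with the Stage 2 heading, so that it is clear whether recruitment is sequential or cumulative.
3. Reword the Design sentence to say that co-interventions will be described to help interpretation, not that this prevents their influence. State calendar-time confounding as a limitation.
4. Optional: if the service evaluation does continue in areas not yet opened, use those surveys as a supplementary concurrent comparison. Its value is limited by the contamination risk raised in the Discussion and by there being no unexposed area in the last fortnight.

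The cost is one field on the survey form and some analysis wording. The downside is fewer responses on each area chart. If area was not captured in the baseline surveys, it may be hard to recover later.

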**Figure 1 F1:**
[figure not shown]
Study design overview. EPR, electronic patient record systems; PEC, parents’ experiences of communication in neonatal care.

### Participants

All eligible parents and neonatal staff members will be approached. Written informed consent will be obtained from all participants.

#### Parents

The lead researcher will recruit parents of babies that are inpatients on the Chelsea and Westminster hospital neonatal unit by directly approaching them on the unit during their baby’s stay. This neonatal unit in London, UK, provides tertiary level neonatal intensive care, including specialist surgical care, with 750 annual admissions and a 36-cot capacity.

*Inclusion criteria:* We will start recruiting parents with babies in the lower intensity part of the unit for 4 weeks (Special Care Baby Unit- SCBU), who are medically stable and not acutely unwell. We will additionally recruit parents in the High Dependency Unit (HDU). area for 2 weeks and parents from the Intensive Care Unit (ICU) area for the final 2 weeks.*Exclusion criteria:* Parents that cannot speak and/or read English will be excluded as the study’s information documents and communication tool are in English. Parents younger than 16 years of age will be excluded.

Recruited parents will be asked to complete a demographic form including their age, gender, ethnic group, infant’s gestational age and infant’s length of stay on the neonatal unit.

#### Neonatal staff members

The lead researcher, in her role as part of the clinical team, will recruit staff members (nurses and doctors) by approaching them on the neonatal unit. Staff of all grades/seniority will be included.

### Outcome measures

#### Primary outcome

The primary outcome is parent satisfaction ‘with communication of clinical information and involvement in care’ and will be measured by a self-administered *Parents’ Experiences of Communication in neonatal care* survey (PEC). The PEC survey is an adaptation of the original UK national Neonatal survey 2014 carried out by the Picker Institute (see online supplementary file 3). We have completed qualitative cognitive survey testing with parents on the Chelsea and Westminster neonatal unit and are currently conducting a survey validation study, using preliminary survey data. The PEC study will be published once validation analysis is completed. The survey contains 35 questions (Likert scale and free text). There are five sections: staff on the neonatal unit (nine questions); information and support for parents (20 questions, six of which specific to *My Baby’s Summary Report*); your involvement in your baby’s care (four questions); leaving the neonatal unit (one question); your comments (one question).

10.1136/bmjpo-2019-000515.supp3Supplementary data

